
### Primary analysis

The primary study hypothesis states that the perioperative administration of NAC is superior to placebo in reducing the severity of postoperative dysfunction, as measured by the CBB at POD 7, and compared with baseline. Analysis of the primary outcome will be via ANCOVA, utilising the baseline psychomotor-attention composite score as a covariate. Assumptions of the ANCOVA will be examined through standard tests and residual plots, with transformation of variables being considered if normality of the residuals is not met. The psychomotor-attention composite is made up of the detection and identification tasks on the CBB and represents the reaction time of the participant, where higher scores indicate lower reaction speed and can be used to suggest the presence of impairment. The composite score is calculated by standardising each task score and adding them together. All analyses will be performed as intent-to-treat, in order to best emulate practice settings.

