### Randomisation, allocation, and concealment

Once consent is confirmed, participants are randomised to a treatment group. Randomisation is stratified by surgery type (orthopaedic or nonorthopaedic) and age (less than 80 years or 80 years or older) to provide four strata for the study. The allocation code was produced by an independent researcher prior to the commencement of recruitment and was generated by a computer-generated list, using permuted block randomisation with variable block sizes. The allocation code is concealed to all trial personnel, with the exception of the dispensing pharmacist. The pharmacist allocates the participant number, based on the relevant stratum and holds the code if unblinding is required, but is not involved in data collection. All other relevant persons, including investigators, research assistants, research nurses, and participants are blind to the treatment allocation until the end of the data analysis.

To aid treatment concealment, all trial materials appear identical. Further, the placebos have been dusted with a nontherapeutic amount of NAC to assist with matching odours (given that NAC has a strong odour). The placebos and NAC capsules are identical in size, taste, and appearance. All trial medication is provided in identical bottles. Any unused medication is returned to the pharmacy for auditing.

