Stratification by age enhances parity between groups in terms of its effects upon cognition, in accordance with established risk factors [5, 37]. Despite the relative safety and success of orthopaedic operations compared with nonorthopaedic operations, the risk of cognitive dysfunction is still significant [3]. Accordingly, orthopaedic patients represent an opportunity to examine potential cognitive change that is less likely attributable to other factors. Additionally, stratification by orthopaedic and nonorthopaedic counteracts the wide variability of reported POCD in the literature [38]. Meta-analyses suggest small cognitive improvements from pooled data yet individual studies note an incidence of POCD as high as 45 % [38]. It is widely held that this variability is due mostly to discrepancies in diagnostic criteria [39] but the concern remains that a significant subset of individuals within the orthopaedic cohort do experience cognitive improvement. The literature to date has not provided the means to identify them prospectively, but it has been suggested that a low cognitive baseline secondary to chronic inflammation, pain, opioid consumption, and restricted mobility, coupled with the potential for surgical remedy, is a potent confounder of postsurgical cognition [40]. This complex and not yet fully characterised surgical profile suggests that the broad classification of surgeries into orthopaedic and nonorthopaedic may help to minimise any confounding in the collected data, with negligible loss of power with respect to a nonstratified design.

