The literature suggests a strong correlation between the two tasks of the psychomotor-attention composite, detection and identification, for simplicity’s sake assumed to be in the region of *r* = 0.8 is expected (for example, see the similarities present on scores from the research of Hammers et al., 2012; [55] and Lim et al., 2012 [56]). Further, the variances for pre and postsurgery will be standardised to 1. The variance of the composite is calculated as the sum of pre and postsurgical variances plus twice the correlation of the composite tasks; 2 + 2 (0.8) = 3.6. Therefore, to estimate the effect of MCI (and by extension, cognitive change after surgery), we divide the combined effect size for the psychomotor-attention composite by the standard deviation of the effect size, that is the square root of the variance of the composite. From Lim et al., the effect of MCI size of the change in reaction speed for the detection and identification tasks were −0.33 and −0.63, respectively, giving a total reduction in reaction speed effect size of −0.96. Therefore, the total effect of MCI (and by extension, cognitive change after surgery) upon the psychomotor-attention composite is equal to: −0.96/√3.6 = −0.51. Given that NAC is unlikely to improve cognition beyond baseline estimates, it is proposed that NAC may instead ameliorate the severity of cognitive dysfunction compared with placebo. Given the limited available data, we have attempted to estimate an approximate protective effect based on the use of NAC in analogous conditions, such as traumatic brain injury [63]. Additionally, it is unrealistic to assume complete prevention of cognitive dysfunction. Therefore, a relative reduction in severity of cognitive dysfunction of 50 % represents an appropriate compromise to calculate the power. Given the likelihood of significant correlation in pre and postsurgery cognition scores, and in the absence of any identifiable correlation size, it is prudent to include an estimation of correlation patterns in the medium range (*r* = 0.50). A protective effect of NAC of 50 % would then set the expected effect of postoperative cognitive change as modulated by NAC at = −0.255. Assuming an alpha level of 0.05, power of 80 %, and a pre and postsurgical score correlation of 0.5, a sample size of 370 participants will have 80 % power to detect a minimum absolute effect size of 0.255 using an analysis of covariance (ANCOVA) model. This sample size includes approximately equal representation across stratification by age and surgery type for intervention.

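### The primary ANCOVA names only the baseline score as covariate and omits the two stratification factors, which makes the test slightly conservative and costs a little precision

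*Protocol article*

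**What the plan says.** In the protocol article, the section on randomisation, allocation and concealment sets up four strata: "Randomisation is stratified by surgery type (orthopaedic or nonorthopaedic) and age (less than 80 years or 80 years or older"). Allocation within them is made "using permuted block randomisation with variable block sizes".

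The same section gives the reasons. For age: "Stratification by age enhances parity between groups in terms of its effects upon cognition, in accordance with established risk factors". For surgery type, it argues that "the broad classification of surgeries into orthopaedic and nonorthopaedic may help to minimise any confounding in the collected data", noting that some orthopaedic patients may improve cognitively after surgery.

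The primary analysis section then names the model and its covariate: "Analysis of the primary outcome will be via ANCOVA, utilising the baseline psychomotor-attention composite score as a covariate". Neither stratification factor appears there. The sample size section mentions the strata only as being represented in the sample, and its power calculation uses only the correlation of 0.5 between scores before and after surgery. Where the secondary ANCOVAs name a covariate, it is the baseline value. Demographic and medical variables come back only in the exploratory subgroup work.

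**The concern.** Blocked randomisation within strata makes the arms more alike on age group and surgery type than simple randomisation would. If those factors predict the day-7 composite beyond the baseline score, the treatment difference varies less from trial to trial than an analysis ignoring the strata supposes. A model without the factors keeps their contribution in the residual variance, so it reports too large a standard error, too wide an interval and too large a p-value.

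The protocol chose these factors because it relates both to the outcome, so the mismatch lies between its own design rationale and its own model. At stake is some precision in a trial whose power, on its own inputs, is barely above 80%.

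**Working it through.** **Inputs.** From the sample size section: alpha 0.05 (sidedness not stated, two-sided taken), power 80%, standardised effect 0.255, variance 1, pre/post correlation r = 0.5, total N = 370 in a 1:1 ratio. Assumed, because the document does not give it: R², the share of residual day-7 variance (after baseline) that age stratum and surgery type explain, taken as 0, 2%, 5% and 10%. Also assumed: 333 analysed, a 10% loss from 370 that leaves the strata balanced.

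**Reproducing the plan's figure.** The residual SD after baseline adjustment is √(1 − 0.5²) = 0.866. The number per arm is 2 × (1.960 + 0.842)² × 0.75 / 0.255² = 181.1, so 182 per arm and 364 in total, within 2% of the stated 370. The power claim for "power to detect a minimum absolute effect size of 0.255 using an analysis of covariance (ANCOVA) model" therefore stands. A one-sided test would need 286 and no baseline adjustment 484, so a two-sided ANCOVA on baseline alone is what was planned. With 370 the power is 80.6% by the noncentral t (80.8% by the normal approximation).

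**Effect of omitting the strata.**

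- Standard error reported by the model without strata: 0.866 × √(4/N), which is 0.0900 at N = 370.
- True standard error under stratified allocation: the same multiplied by √(1 − R²), for example 0.0854 at R² = 10%.
- Ratio of reported to true: k = 1/√(1 − R²). The interval is too wide by k − 1.
- True type I error with strata omitted: 2 × P(Z > 1.96k).
- Power omitted: chance that a noncentral t with noncentrality 0.255/(true SE) exceeds k × the critical value.
- Power included: the same noncentrality against the ordinary critical value.

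Results at N = 370:

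| Assumed R² | Interval too wide by | True type I error, omitted | Power, omitted | Power, included | Gain (points) |
|---|---|---|---|---|---|
| 0 | 0 | 0.050 | 80.6% | 80.6% | 0 |
| 2% | 1.0% | 0.048 | 80.9% | 81.4% | 0.5 |
| 5% | 2.6% | 0.044 | 81.2% | 82.6% | 1.3 |
| 10% | 5.4% | 0.039 | 81.9% | 84.5% | 2.7 |

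Gains are taken from unrounded powers. With 333 analysed and R² = 10%, power is 77.6% omitted and 80.6% included.

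**Simulation check.** 20,000 trials of 370 patients were run with blocks of 4 and 6 in four strata, assuming 20% aged 80 or over and 50% orthopaedic. At R² = 5%, type I error was 0.043 omitted against 0.048 included, and power 81.0% against 82.4%. At R² = 10%, the figures were 0.038 against 0.048, and 81.6% against 84.4%. These agree with the formulas.

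**The case against.** The article condenses a fuller plan. The sentence on the primary model does not say that no other covariate will be used, and an analysis plan that is not shown may add the strata. This limits confidence but does not remove the point: the article is not silent on covariates. It names the one the model will use, and adding the strata would change the published model.

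The size rests on an unknown. Age-related slowing is probably already present in the baseline reaction-time score, so a cut at 80 years may add little beyond it. The text on surgery type is also guarded: it attributes most of the reported variability to differing diagnostic criteria. This stands, and it is why the result is given as a range that starts at zero.

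A reader might infer more than the document supports:

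- **That the inference is invalid or anti-conservative.** It is not. The estimate is unbiased and the error rate lies at or below 0.05.
- **That the benefit of stratifying is lost altogether.** It is not. The estimate keeps its balance and its smaller sampling variance; only the reported standard error fails to show it.
- **That adjustment would gain 3.9 points at R² = 10%, from 80.6% to 84.5%.** That comparison holds the omitted-strata power fixed, although stratified allocation raises it to 81.9%. The gain is 2.7 points.
- **That the sample size is wrong.** It reproduces on the protocol's own inputs.

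**Conclusion.** The point holds as a modest one. The protocol stratifies on two factors it relates to postoperative cognition and then specifies a primary model without them. The consequence is a conservative test and a slightly wide interval: up to about 5.4% too wide and 2.7 points of power at the largest share considered, and nothing if the strata explain no variance beyond baseline. These sizes assume two-sided testing, the protocol's effect of 0.255 and correlation of 0.5, and an R² that the document does not supply. The loss matters a little more if fewer patients are analysed: at 333 and a 10% share, including the strata separates 80.6% power from 77.6%. This should be corrected because correction is nearly free, not because the planned result would be unsound.

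**What to change.** State the primary model as the day-7 composite regressed on treatment, baseline composite, surgery type (orthopaedic or not) and age stratum (below 80, or 80 and over). Use the same two terms in the secondary ANCOVA and mixed models. If an analysis plan already includes them, align the two documents.

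The cost is one line of wording and two of the 367 residual degrees of freedom (370 less intercept, treatment and baseline). It needs no extra participants, and both factors are already recorded for randomisation. Fixing the terms before unblinding also removes any later choice between adjusted and unadjusted results. Using continuous age in addition, or replacing the chi-square tests for delirium and mood with stratified logistic regression, is optional and not needed to settle this point.

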### Secondary analyses

Linear mixed-model ANCOVA will be conducted to model the differences in cognitive changes between treatment groups by fitting a linear curve to represent the relationship between performance on tasks and time point. The magnitude of the differences between treatment groups will be expressed as Cohen’s *d*.

Between-group differences on the individual tasks of the neuropsychological battery will be examined. Similar to the primary analysis, an ANCOVA will be used to examine the performance of participants on each of the neuropsychological battery tasks. Included in the analyses will be the individual CBB tasks, detection, identification, one-card back, and one-card learning; RBANS tasks, the COWAT, and Trail Making Tests A and B. Data will be represented as a linear mixed-effects model, comparing the performance of the NAC group compared to the control group over time. The magnitude of difference between treatment groups will be calculated as Cohen’s *d*.

Between-group differences on measures of delirium and mood dysfunction will be analysed using a chi-square test using the CAM and HADS measures. Participants will be classified dichotomously as displaying symptoms of delirium or mood dysfunction according to established cut-off points; 11 points on either anxiety or depression for the HADS, or fulfilment of delirium criteria according to the CAM.

Between-group differences on measures of quality of life will be analysed using an ANCOVA to examine changes over the course of the trial, controlling for baseline values as a covariate. Between-group differences will be examined for change across time from baseline scores to 3 months and 12 months. A linear mixed-effects model will be used to represent the data comparing treatment groups, with the magnitude between treatment groups expressed as Cohen’s *d*.

Between-group differences in serum levels of biological markers will be examined prior to surgery and at POD2 in order to capture the surgical stress response. An ANCOVA will be performed to examine the between-group differences over time, with baseline values acting as a covariate. Data will be graphed using a linear mixed-effects model, with the magnitude of difference between treatments groups expressed as Cohen’s *d*.

A bivariate correlation analysis exploring serum biological marker levels and cognitive function will be calculated for each of the battery tasks.

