## Background

Cognitive decline after surgery is common amongst elderly surgical patients [1–3]. Postoperative cognitive dysfunction (POCD) refers specifically to dysfunction in postoperative cognitive performance relative to presurgical performance; however, the exact threshold delineating when cognitive decline can be classified as POCD varies considerably within the literature [4]. One of the most robust studies places the early postoperative incidence rate of POCD at approximately 25 % of major surgery patients, aged over 60 years [1, 3, 4], and research suggests that patients aged at least 60 years are at significantly greater risk compared to younger patients [37]. Generally, cognitive decline after surgery manifests as subtle dysfunction across a number of cognitive domains, such as memory, attention, and psychomotor function. It may persist in some patients for months or years and herald the onset of a dementia process, to the significant detriment of quality of life [5–8]. Given the lack of consensus regarding the exact demarcation of POCD, it is useful to refer instead to an absolute difference in cognitive function after surgery controlling for baseline values, regardless of whether or not such a change in function meets the specifications for POCD.

At present, there are neither pharmacological interventions nor preventative agents for POCD. The role of oxidative stress and neuroinflammation as a result of a surgical stress response is well-characterised, and now provides a potentially modifiable target for therapeutic intervention [9–13]. Developing evidence suggests that there is a relationship between surgery and anaesthesia and the production of inflammatory signals and reactive oxygen species in the periphery and the brain which are associated with cognitive dysfunction [14–19].

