### Dose and treatment regimen

Administration of NAC in a wide variety of medical settings has been shown to be safe [41, 42]. Whilst there is variation within the literature regarding dose and timing of NAC, recent reviews have suggested NAC administered per os at doses of 2400 mg/day to be efficacious in delivering demonstrable biomarker change with a negligible adverse effect profile [43, 44]. Kuyumcu et al. [33] showed improved oxidative status in abdominal surgery patients with a total dose of 2400 mg of NAC administered intravenously over 2 days prior to surgery. Dose regimens well in excess of 2400 mg/day have been safely explored with some regularity, but are likely to be burdensome during oral administration, a route which offers greater safety [62] and ease of administration than intravenous infusion. Bearing in mind the previously established effective doses, the expected duration of the surgical stress response [42], the oral bioavailability of NAC and the relative ease, safety and cost effectiveness of oral administration, we have chosen a regimen of 1200 mg NAC administered per os twice daily, consisting of two 600-mg capsules in the morning and again in the evening, starting on the day of surgery and continuing for 4 days to a total cumulative dose of 9600 mg. Administration takes place during the patients’ regular morning and evening drug rounds, facilitated by the ward staff and recorded from the patient chart by the research nurses. Placebo is administered in an identical fashion. Medication is dispensed by the pharmacy and administration coordinated by the research nurses, and recorded in the trial records for each participant. Unused medication is returned to the pharmacy for disposal. Episodes of nausea and vomiting are recorded by research staff.

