### Cognitive function measures

Cognitive function is assessed prior to surgery, 7 days post surgery, 3 months post surgery, and again 12 months post surgery. Cognitive dysfunction at approximately 1 week post surgery has been shown to be a significant predictor of further cognitive change in elderly postsurgical patients, and so comparisons of cognition at postoperative day (POD) 7 with preoperative baseline is considered the primary outcome [37]. A number of cognitive domains are measured using a selection of validated neuropsychological tests. All assessments are reliable and validated for the use in detecting cognitive change [45–51, 61, 62]. All assessments, with the exception of the CBB, are recorded in specially created Case Report Forms, and stored securely after the transcription of data into the secure computer database (Research Electronic Data Capture, REDCap). The CBB automatically uploads data into a secure database, and does not require paper records. All assessments are performed by trained research staff, supervised for compliance and quality by the senior clinicians. Psychomotor, attention, learning, and working memory domains are assessed with the computerised CBB. The CBB consists of four tasks: detection, identification, one-card learning, and one-card back. In the detection task, the participant is asked to press a button as soon as a displayed card is turned over. The psychomotor-attention composite is made up of the detection and identification tasks on the CBB and represents the reaction time of the participant, where higher scores indicate lower reaction speed and can be used to suggest the presence of impairment. The CBB has shown efficacy in detecting cognitive change in healthy participants over 12 months [60], and in clinical samples. [45]. Immediate memory, visuospatial, and delayed memory domains are assessed with the Repeatable Battery for the Assessment of Neuropsychological Status (RBANS) [46]. The RBANS consists of 12 subtests measuring immediate and delayed verbal and visuospatial memory, and is commonly used for the detection of cognitive change [46]. Alternate forms are used at each assessment.

Verbal fluency and executive function is assessed with the Controlled Oral Word Association Test (COWAT). Over three attempts, participants are given 1 minute to list as many words beginning with a specified letter. Errors and perseverations are recorded [47].

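### The secondary cognitive model fits a straight line through baseline, day 7, 3 and 12 months, which gives biased answers to hypotheses about individual visits

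*Protocol article*

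**What the plan says.** The Protocol article fixes the form of the longitudinal cognitive model under Secondary analyses: "Linear mixed-model ANCOVA will be conducted to model the differences in cognitive changes between treatment groups", and it does so "by fitting a linear curve to represent the relationship between performance on tasks and time point". The article mentions no categorical visit term, piecewise line or other non-linear time term.

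The schedule is given under Cognitive function measures: "Cognitive function is assessed prior to surgery, 7 days post surgery, 3 months post surgery, and again 12 months post surgery". The secondary hypotheses (Hypotheses) claim superiority on the psychomotor-attention composite at 3 months and at 1 year, and on the rest of the battery at day 7, 3 months and 1 year. Outcome variables says that comparisons with baseline will be made at each time point.

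The primary analysis is separate and uses day 7 only: "Analysis of the primary outcome will be via ANCOVA, utilising the baseline psychomotor-attention composite score as a covariate".

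**The concern.** The trial's own rationale does not describe a straight line. Treatment is short, "starting on the day of surgery and continuing for 4 days", and the primary hypothesis concerns an early effect. Of the decline itself, Background says: "It may persist in some patients for months or years". For other patients it therefore does not persist. The expected course is a drop by day 7 followed by recovery or persistence, and neither is linear from baseline.

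The spacing adds to the problem. Day 7 lies at about 0.23 months on a 12-month axis, almost on top of baseline, so the 12-month value has most of the leverage on the slope and the line can barely separate day 7 from baseline.

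At stake are the secondary cognitive conclusions, above all for the composite at 3 and 12 months. The ANCOVA in the next paragraph of Secondary analyses is for the individual tasks, so the straight-line model is the only analysis stated for the composite at the late visits.

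**Working it through.** **Inputs from the article.** Visits at 0, 7/30.4 = 0.23, 3 and 12 months. Effect size d = 0.255 SD. 370 participants allocated 1:1, so 185 per arm. "Assuming an alpha level of 0.05, power of 80 %, and a pre and postsurgical score correlation of 0.5"; sidedness is not stated and two-sided is taken. On the composite the direction is "where higher scores indicate lower reaction speed", so signs are turned here to make positive values favour NAC.

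**Assumptions, not in the article.** Outcome SD 1, correlation 0.5 between every pair of visits (the article gives it only for pre and post surgery), no dropout, and the benefit patterns below.

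**Step 1: the plan's own figure.** n per arm = 2(1.96 + 0.842)²(1 − 0.5²)/0.255² = 2 × 7.85 × 0.75/0.0650 ≈ 181, rounded up to 182, or 364 in total (366 with the noncentral t). This is close to the stated 370. With 185 per arm, z = 0.255/√(2 × 0.75/185) = 2.83 and power is Φ(2.83 − 1.96) = 81%. The day-7 ANCOVA reproduces. The article gives no figure for the longitudinal model.

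**Step 2: the straight line with all four visits as responses.** Mean time is 15.23/4 = 3.81. The sum of squares of time is 14.50 + 12.80 + 0.65 + 67.12 = 95.07. The expected slope difference is Σ(t − 3.81) × difference / 95.07. Its standard error is √(2(1 − 0.5)/(185 × 95.07)) = 0.00754.

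*Fading benefit (0, 0.255, 0.1275, 0).*
- Slope = (−3.58 × 0.255 − 0.81 × 0.1275)/95.07 = −0.0107 SD per month.
- z = −1.42. The chance of significance is Φ(−1.96 + 1.42) = 29% in favour of placebo and about 0.04% in favour of NAC.
- Intercept = 0.0956 + 0.0107 × 3.81 = 0.136.

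*Sustained benefit (0, 0.255, 0.255, 0.255).*
- Slope = 0.255 × 3.81/95.07 = 0.0102 per month; z = 1.35, power about 27%.
- Intercept = 0.191 − 0.0102 × 3.81 = 0.152.

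True and fitted differences:

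| | Baseline | Day 7 | 3 months | 12 months |
|---|---|---|---|---|
| Fading, true | 0 | 0.255 | 0.128 | 0 |
| Fading, fitted | 0.136 | 0.134 | 0.104 | 0.008 |
| Sustained, true | 0 | 0.255 | 0.255 | 0.255 |
| Sustained, fitted | 0.152 | 0.155 | 0.183 | 0.275 |

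Both lines show a baseline difference that randomisation rules out in expectation.

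**Step 3: baseline as covariate only (day 7, 3 and 12 months as responses).** Mean time is 5.08 and the sum of squares is 75.74. Under fading, the slope is (−4.85 × 0.255 − 2.08 × 0.1275)/75.74 = −0.0198 per month, z = −2.35, significant in favour of placebo 65% of the time. Under a sustained benefit the slope difference is exactly zero, so a slope test has no power for it.

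**Step 4: where the sign reversal stops.**
- Fade only to half (0.255, 0.191, 0.128), four visits: slope −0.0009d per month, in effect zero; coded by visit number, +0.125d per visit.
- Full fade with four visits coded 0 to 3: slope −0.05d per visit, but significant in favour of placebo only 5.8% of the time.
- Benefit held to 3 months and then gone, four visits coded 0 to 3: slope zero.
- Fade only to half with baseline as covariate: slope −0.039d per month, but the fitted differences stay positive (0.239, 0.212, 0.123).

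**Step 5: visit as a categorical factor.** The model returns the true difference at each visit. The day-7 contrast keeps about 81% power under the same assumptions.

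**The case against.** The strongest reply is that the article never names the group-by-time slope as the contrast tested. It speaks of differences in cognitive change and reports Cohen's d. A group main effect from the same model would show some average benefit. In the four-visit model under fading, every fitted difference in the table is at or above zero, so the negative slope only describes a benefit that shrinks to nil. This stands: the slope results are conditional on the slope being the test. It does not rescue the fitted differences, which are about half the true value at day 7 under fading, and too small at day 7 and 3 months under a sustained benefit.

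Second, the late hypotheses posit an enduring benefit, so a pattern that is nil at 1 year is not the effect those hypotheses look for. This also stands. But under an enduring benefit the slope has either low power (27%) or none.

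Third, Outcome variables promises comparisons at each time point, and the individual tasks have an ANCOVA modelled on the primary one. That limits the point for the tasks. It does not help the composite at 3 and 12 months.

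Fourth, a reader might multiply the sustained-benefit slope by 12 and conclude that the model recovers only 0.12 of a true 0.255. That leaves out the fitted intercept difference of 0.152; the line gives 0.275 at 12 months.

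**Conclusion.** The stated linear time term is a poor choice for the cognitive outcomes and should be replaced. Under the assumptions listed, a full fade gives a fitted day-7 difference of about 0.13 instead of 0.255. It also gives a slope of -0.011 SD per month that is significant in favour of placebo about 29% of the time, if the slope is tested with all four visits and time in months. A sustained benefit gives 0.155 at day 7 and 0.183 at 3 months.

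A reader might infer that any early benefit that fades will appear as harm, or that the trial's efficacy conclusions rest on this model. The documents support neither. With four visits the reversal needs the benefit to fade to about nil, and it depends on how time is coded and on which contrast is tested. The primary day-7 ANCOVA, the sample size and the data collection are untouched. Nor does the point cover every longitudinal model in the article. The straight line is stated once, for cognition; a linear mixed-effects model need not be linear in time, the WHOQOL-BREF has no day-7 visit, and the biomarkers have only two times. This is a secondary-analysis point of lower severity.

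**What to change.** For the CBB composite and the cognitive battery, replace the linear time term by visit as a categorical factor (day 7, 3 months, 12 months). Include treatment, treatment-by-visit, baseline-by-visit and the stratification factors (age group and surgery type), with an unstructured covariance. Report the adjusted treatment difference at each visit; this answers the secondary hypotheses as they are worded. If the same approach is used for the WHOQOL-BREF, include only the 3- and 12-month visits.

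The cost is a change of wording and a few extra model parameters per outcome. No further data or participants are needed. The change should be made before unblinding, so that the form of time is not chosen from the results.
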